### Statistical Methods

#### Statistical Methods for Primary and Secondary Outcomes

Subjects will be classified using logistic regression or another classifier (such as support vector machines or linear discriminant analysis) as predicted responders or non-responders. The predicted outcomes will be compared with real-life outcomes to determine the accuracy, sensitivity, and specificity of our statistical model. The accuracy will be calculated as the proportion of correctly predicted responders and correctly predicted non-responders within the whole analyzed population. The minimum clinically significant accuracy was set to 70%. The sensitivity of the model will be expressed as the proportion of predicted responders within all real-life responders. The specificity of the model will be expressed as the proportion of predicted non-responders within all real-life non-responders.

Differences in the EEG power spectra between real-world/predicted responders vs. non-responders will be examined using two-sample *t*-test or Mann-Whitney test, as applicable.

As a level of statistical significance, α = 0.05 will be used for all statistical tests.

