Our group developed and validated a statistical model (Pre-X-Stim) for the prediction of VNS efficacy (6). This algorithm is based on the analysis of routine scalp electroencephalogram (EEG) data, which is the main advantage of our approach because it is an inexpensive, easily-accessible method with minimal burden on the patient. When summarizing the procedure in brief, we retrospectively identified pre-implantation routine scalp EEG recordings in patients treated with VNS for drug-resistant epilepsy. The patients were characterized as responders or non-responders based on the long-term outcomes. The EEG recordings were segmented into several time intervals. In each interval, the changes of dynamics in EEG power spectra were calculated. Based on these changes, the statistical classifier for a prediction of VNS efficacy was developed (Patent No. EP 3437692). The validity of the model was verified on an independent data set, in which it was able to predict the response to VNS with 86% accuracy, 83% sensitivity, and 90% specificity. The usability of this model with different EEG systems was subsequently proven (7). Our previous studies were, however, retrospective and monocentric, and these are the crucial limitations that we would like to overcome with the proposed project, PRECISE (PRediction of vagal nerve stimulation EfficaCy In drug-reSistant Epilepsy).

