### Objectives

The study is designed to determine the availability of VNS prediction based on pre-implantation data. The main goal is to validate Pre-X-Stim in a real-life prospective study.

The primary aim of our study is to evaluate whether we are able to predict VNS efficacy in an individual patient based on the pre-implantation scalp EEG. We defined two hypotheses:

We hypothesize that there are differences in the dynamics of EEG power spectra in response to activation methods (eye-opening/closing, photic stimulation, hyperventilation) between responders and non-responders to VNS therapy.We hypothesize that we can predict the patient's response to VNS therapy in terms of responder vs. non-responder by our statistical model based on the changes in the dynamics of EEG power spectra.

Based on these hypotheses the primary and secondary endpoints were established. Primary endpoint involves the accuracy of the statistical model for prediction of response to VNS therapy in terms of responders and non-responders in drug-resistant epilepsy, evaluated after 2 years. Secondary endpoints include (1) the quantification of differences in EEG power spectra (Relative Mean Power, %) between real-life responders and real-life non-responders to VNS therapy in drug-resistant epilepsy; (2) prediction of patients' response to VNS therapy in terms of responders (≥50% seizure reduction from baseline) and non-responders (<50% seizure reduction from baseline). Each endpoint will be evaluated 2 years after recruitment.

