### Protocol for EEG Recording

The EEG will be recorded on the EEG recording system with a sampling frequency of 250 Hz or higher, with electrodes placed on the scalp according to the 10–20 system (with the following electrodes: Fp1, Fp2, F7, F3, Fz, F4, F8, T3, C3, Cz, C4, T4, T5, P3, Pz, P4, T6, O1, and O2). Different electrode names are allowed, but their position must correspond with the position of the previously defined electrodes. Additional electrodes are also allowed, but will not be evaluated within the study. EEGs with fewer or differently-positioned electrodes are not allowed.

The EEG is recorded in a supine position with eyes closed, except for periods with opening of eyes. The recorded EEG will have a duration of 20 min or more and must contain defined segments in the following order as in Table 1.

**Table 1 T1:** Predefined segments ordering in the course of EEG recording.

Segment 1	Rest 1	duration at least 2 min
Segment 2	Eyes opening/closing	duration at least 10 s
Segment 3	Rest 2	duration at least 10 s; immediately after eye closure
Segment 4	Photic stimulation	stimulation frequencies: 5 Hz (10 s)−10 Hz (10 s)−15 Hz (10 s)−20 Hz (10 s)−25 Hz (10 s)−30 Hz (10 s)−25 Hz (5 s)−20 Hz (5 s)−15 Hz (5 s)−10 Hz (5 s)−5 Hz (5 s); light intensity at least 0.7 Joule
Segment 5	Hyperventilation	duration at least 4 min (2 min hyperventilation by nose + 2 min hyperventilation by mouth)
Segment 6	Eyes opening/closing	duration at least 10 s
Segment 7	Rest 3	duration at least 10 s, immediately after eye closure
Segment 8	Rest 4	duration at least 2 min

The recorded EEG will be anonymized and labeled by a unique code previously attributed to a patient. In the next step, the EEG will be sent for mathematical/statistical processing. Based on this processing, the patients' predicted response to VNS will be determined in terms of predicted responders (seizure reduction ≥50%) vs. predicted non-responders (seizure reduction <50%). Neither the patient nor the physician will be informed about the classification results.

Two assessments are designed for patients' follow-up:

Assessment 1−1 year after stimulation initialization, and

Assessment 2−2 years after stimulation initialization.

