### Outcomes

The primary outcome of the study is the accuracy of the statistical model for prediction of response to VNS therapy in drug-resistant epilepsy, expressed as a percentage of correct predictions (responders vs. non-responders), evaluated after 2 years.

The secondary outcomes of the study are the quantification of differences in EEG power spectra (Relative Mean Power, %) between real-life responders and real-life non-responders to VNS therapy in drug-resistant epilepsy and the prediction of patients' response to VNS therapy in terms of responders, expressed as sensitivity of the model, and non-responders expressed as specificity of the model. If possible, these data can be used for further improvement of the statistic model.

The study is concerned with the verification of the real-life validity of our statistical classifier for the prediction of VNS response based on pre-implantation EEG data. The patients will be classified based on their predicted response as predicted responders (≥50% seizure reduction) and predicted non-responders (<50% seizure reduction). In Assessments 1 and 2, respectively, the patients' real-life response will be determined: real-life responders (≥50% seizure reduction) vs. real-life non-responder (<50% seizure-reduction). The predicted and real-life responses will be statistically compared in terms of accuracy, sensitivity, and specificity.

The individual patients' groups (predicted responders vs. predicted non-responders, real-life responders vs. real-life non-responders) will be compared based on their demographic data, health history, ASM, and VNS parameters. A suitable statistical test will be chosen concerning the characteristics of the data (Pearson's Chi-squared test for categorical variables, and Wilcoxon-Mann-Whitney test for continuous variables).

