### Sample Size

The sample size was estimated for the primary endpoint, which was defined as the accuracy of the statistical model for prediction of response to VNS therapy in terms of responders and non-responders in drug-resistant epilepsy. During the verification of the validity on the independent dataset, the model was able to predict the response to VNS with 86% accuracy. The minimal clinically significant accuracy was set to 70%. The sample size is estimated for the following hypothesis:

Hypothesis H0: *p* = 0.7 vs. Hypothesis H1: *p-value* > 0.7.

At the level of significance α = 0.05 and with a power of 90%, the number of patients needed for the analysis of the primary endpoint is 57. Assuming a drop-out rate of 50%, a total number of 114 patients should be enrolled.

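### The planned test of EEG power spectra between predicted responders and predicted non-responders is circular and lies outside the defined secondary endpoint; the real-life comparison is sound

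*Protocol article*

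**What the plan says.** **The test.** The protocol article, Statistical Methods for Primary and Secondary Outcomes, plans: "Differences in the EEG power spectra between real-world/predicted responders vs. non-responders will be examined using two-sample" t-test or Mann-Whitney test, as applicable. The slash joins two groupings of the same patients, by real outcome and by predicted outcome. The section closes with: "As a level of statistical significance, α = 0.05 will be used for all statistical tests".

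**How the predicted groups arise.** Background and Rationale describes calculating changes in EEG power-spectra dynamics across intervals of the recording, and continues: "Based on these changes, the statistical classifier for a prediction of VNS efficacy was developed". The second hypothesis in Objectives says that response is to be predicted "by our statistical model based on the changes in the dynamics of EEG power spectra". Protocol for EEG Recording confirms that the predicted class results from processing the study EEG.

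**The endpoint.** Outcomes defines the spectral secondary outcome as "quantification of differences in EEG power spectra (Relative Mean Power, %) between real-life responders and real-life non-responders to VNS therapy". The Abstract and Objectives also define it by real-life response only. The predicted-group comparison of spectra appears in the Statistical Methods section and in none of these definitions.

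**The concern.** A two-sample test has a meaningful null hypothesis when group membership is determined independently of the variable compared. Here the predicted label is a function of the patient's EEG spectra. Patients are sorted by their spectra and then compared on their spectra, so a difference is built in. It shows what the classifier separates and carries no information about response to VNS.

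The first hypothesis in Objectives is that responders and non-responders to VNS differ in EEG power-spectra dynamics. If predicted-group p-values are reported beside the real-life ones, under a heading that covers the secondary outcomes, a result that could hardly fail may be read as evidence for that hypothesis. The article does not set this test apart as exploratory, and Methods for Additional Analyses says that no additional analysis is planned.

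**Working it through.** **1. Sample size used for illustration.** The plan gives no figure for the spectral tests, so its primary sample size is used. Inputs from Sample Size: null accuracy 0.70, expected accuracy 0.86, α = 0.05 (one-sided, from the direction of the alternative), power 90%.

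n = [(1.645 × √(0.70 × 0.30) + 1.282 × √(0.86 × 0.14)) / 0.16]² = [(0.754 + 0.445) / 0.16]² ≈ 56.1, rounded up to 57. With 50% drop-out, 57 / 0.5 = 114. Both stated figures are reproduced.

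**2. Predicted groups when EEG is pure noise.** Assumptions, because the article gives neither the features nor their weights: m independent standard normal features, equally weighted; predicted class is the sign of their sum; groups of about equal size. For any one of these features:

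- difference in group means = 2√(2/π) / √m
- within-group SD = √(1 − (2/π)/m)
- standard error = SD × √(4/n)
- rejection rate ≈ Φ(t − critical value), with critical value 2.004 at n = 57

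| m | Mean difference | SD | Expected t (n = 57) | Rejection, formula | Rejection, simulation |
|---|---|---|---|---|---|
| 1 | 1.596 | 0.603 | 10.0 | 100% | 100% |
| 4 | 0.798 | 0.917 | 3.29 | 90% | 90% |
| 8 | 0.564 | 0.959 | 2.22 | 59% | 59% |
| 16 | 0.399 | 0.980 | 1.54 | 32% | 33% |

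The nominal rate is 5%. The simulation column rests on 4,000 trials per row.

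**3. Wider null simulation.** This used 1,500 trials per setting, n = 57 or 114, 8 or 32 spectral features of which 1, 3 or 8 feed the classifier, correlation 0 or 0.5 between features, and real outcome assigned at random with 50% responders.

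- *Predicted groups, classifier features:* rejection per feature was 58% to 100% at n = 57 and 87% to 100% at n = 114. At least one significant difference appeared in every trial.
- *Predicted groups, features outside the classifier:* about 5% when uncorrelated with the classifier features, and 89% to 100% at correlation 0.5.
- *Real-life groups:* 4.5% to 5.6% per test, which is the nominal level.

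**4. Several real-life tests at 0.05.** The article states no number of tests. For k independent tests the chance of at least one false positive is 1 − 0.95^k. If k = 8 (an assumption), this is 1 − 0.95⁸ = 34%; in the simulation with 8 features at correlation 0.5 it was 23% to 27%. For comparison, a Bonferroni level of 0.05 / 8 = 0.00625 gives 1 − (1 − 0.00625)⁸ = 4.9%.

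**The case against.** The strongest reply is that the circular comparison rests on one word in one sentence. It is in no endpoint definition, and nothing says that it will be used to support the first hypothesis. Beside the real-life comparison it could serve simply to show what the classifier separates. That is a fair description of a useful display, but such a display needs no p-value, and the article plans a significance test.

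A reader might go further and infer that the first hypothesis and the spectral secondary endpoint would be supported almost whatever the truth. The documents do not support that. Both concern actual response. Real-life status comes from reported seizure frequency compared with the pre-implantation frequency, and neither patient nor physician is told the prediction. That comparison is not circular, and step 3 shows the nominal error rate for each test.

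A reader might also multiply the 19 electrodes by the 8 segments of Table 1 and infer 152 planned tests, or more with frequency bands. The electrodes and segments are requirements for the recording; no section says that each will be tested. Choosing the features and any adjustment is commonly left to an analysis plan, which is not shown, and unadjusted secondary tests are not an error in themselves. This part of the objection stands.

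Finally, the simulated sizes depend on assumed features and weights. The article also does not say that Relative Mean Power is exactly what enters the classifier. Both points limit how far the size can be stated. They do not change the direction as long as the tested spectra are classifier inputs or are correlated with them, which is likely because both come from the same recording.

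**Conclusion.** The point holds in a limited form. The inferential comparison of EEG spectra between predicted responders and predicted non-responders is circular, and it departs from the secondary endpoint as the article defines it. Its p-values will tend to be significant with no true link between EEG and VNS response: 33% to 100% per classifier feature at n = 57 in the settings tried, against 5%. The true rate cannot be given, because the number, weighting and correlation of the classifier features are not stated.

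The real-life spectral comparison is valid test by test. Its familywise error exceeds 5% if several spectra are tested at an unadjusted 0.05, but it cannot be quantified without the number of tests; 34% for 8 independent tests is only an example. The primary endpoint and its sample size of 57 analysed and 114 enrolled are untouched. The planned comparison of predicted groups on demographic data, health history, medication and VNS parameters is not circular in this way, since the article does not describe these as classifier inputs.

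**What to change.** In Statistical Methods for Primary and Secondary Outcomes:

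1. Restrict inferential tests of EEG power spectra to real-life responders versus real-life non-responders, in line with Objectives and Outcomes.
2. Show spectra by predicted group descriptively only, without p-values, and state that they are not evidence for the first hypothesis.
3. Qualify the blanket rule that "α = 0.05 will be used for all statistical tests": report the real-life spectral tests as unadjusted and exploratory, unless a small set of spectral contrasts is named in advance and adjusted for multiplicity.

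The cost is a few sentences and the loss of p-values for the predicted-group comparison. If a contrast set is adjusted, each contrast in it also loses some power. Data collection and the sample size do not change.

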#### Interim Analyses

Not applicable. Interim analysis is not planned.

#### Methods for Additional Analyses (e.g. Subgroup Analyses)

Not applicable. Additional analysis is not planned.

#### Methods in Analysis to Handle Protocol Non-adherence and Any Statistical Methods to Handle Missing Data

No analysis populations are defined for this study. Protocol non-adherence will be assessed by the principal investigator case by case. Patients with major protocol deviations will be excluded from the analysis.

Missing data are not planned to be imputed. However, in the event of substantial missing data for any parameter, a sensitivity analysis using any method of imputation could also be used.

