The patients will be evaluated 1 and 2 years after the start of VNS therapy. The patient will be requested to report any changes in health history, including psychiatric disease, and specific requests will be focused on changes in medication (ASM and other drugs), VNS parameters settings, and seizures. The patients will be asked whether unexpected events influenced their clinical response. If these unexpected events are regarded as “clinically highly important” (such as non-compliance or other newly-diagnosed disease worsening epilepsy), the patient can be excluded based on clinical decision. The data on seizure frequency will be collected by reviewing the patient's diary. The reported seizure frequency will be compared with pre-implantation seizure frequency, and real-life response will be calculated in terms of real-life responders (seizure reduction ≥50%) or real-life non-responder (seizure reduction <50%). The patients will fill in a questionnaire focusing on the quality of life. If the patient does not tolerate at least the minimal VNS settings (0.75 mA) because of serious adverse events, they will be excluded from further analysis (the patient's data will be reported separately). The patients included in our study will be managed according to the best clinical praxis, i.e., the change of ASM and VNS parameters will be done based on the clinicians' decision to reflect the real-life response.

The information collected in Assessments 1 and 2, including real-life response to VNS, will be labeled with the patient's unique code and sent to the coordinating center, where it will be compared with the patient's predicted response.

At the end of Assessment 2, patients will be asked if they are interested in the predicted response to VNS. If the answer is yes, the study physician will contact the coordinating center, where the predicted response for a given patient will be conveyed. The patient will be informed about the predicted response by telephone or during a regular visit (not a part of the study protocol, described below).

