### Assignment of Interventions: Blinding

#### Who Will Be Blinded?

Not applicable. This study is not blinded.

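### Exclusions from the accuracy analysis are left to case-by-case judgement, with no requirement that the person deciding be unaware of the predicted class, so the primary endpoint could be inflated

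*Protocol article*

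**What the plan says.** All references are to the protocol article.

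- **Endpoint.** Under Outcomes, accuracy is "expressed as a percentage of correct predictions (responders vs. non-responders), evaluated after 2 years". Under Statistical Methods for Primary and Secondary Outcomes it is "the proportion of correctly predicted responders and correctly predicted non-responders within the whole analyzed population". The denominator is therefore what is left after exclusions.
- **Exclusion for deviations.** The section on non-adherence and missing data states that no analysis populations are defined, and continues: "Protocol non-adherence will be assessed by the principal investigator case by case. Patients with major protocol deviations will be excluded from the analysis". It gives no list of major deviations, no timing and no masking.
- **Exclusion for unexpected events.** The follow-up text under Protocol for EEG Recording has patients asked, at Years 1 and 2, whether unexpected events affected their response. For events judged highly important, the examples and the consequence read: "non-compliance or other newly-diagnosed disease worsening epilepsy), the patient can be excluded based on clinical decision".
- **Exclusion for intolerance.** Patients who do not tolerate the minimal stimulation setting because of serious adverse events leave the analysis and are reported separately. This rule is stated in advance.
- **Who holds what.** Study Setting gives the coordinating center the EEG analysis and the reporting. The follow-up text says that the information from Assessments 1 and 2 is "sent to the coordinating center, where it will be compared with" the predicted response. Data Management has the statistician analyse the data together with a principal investigator.
- **Masking.** "Neither the patient nor the physician will be informed about the classification results" (Protocol for EEG Recording). Under Who Will Be Blinded?: "Not applicable. This study is not blinded".

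**The concern.** The study is meant to be a prospective validation of a classifier that the same group developed, and its primary result is one proportion tested against 70%. If a person who knows both the predicted and the actual class may decide which patients count, removing a discordant patient raises that proportion directly. Nothing in the non-adherence section rules this out. The protocol does not leave the matter open for another document to settle: it says that no populations are defined and sets a discretionary rule in their place. The sample size already allows for 50% drop-out, so a few selective exclusions would be hard to notice among the other losses.

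**Working it through.** **Inputs.** From Sample Size: null accuracy 0.70, expected accuracy 0.86, α = 0.05, power 90%, 57 patients analysed, 114 enrolled at 50% drop-out. The alternative is accuracy above 0.70, so the test is taken as one-sided. From the Introduction: sensitivity 83% and specificity 90% in the earlier independent data set. The documents give no expected number of exclusions, so every count below is an assumption.

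**Step 1: reproduce the plan's figure.** The exact one-sided binomial test rejects when P(X ≥ x | n, 0.70) ≤ 0.05. For n = 57 the smallest such x is 46 (80.7%), with P(X ≥ 46 | 57, 0.70) = 0.0486 and power P(X ≥ 46 | 57, 0.86) = 0.906. This is the smallest n with at least 90% power, and 57 / (1 − 0.5) = 114. The plan's numbers are correct.

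**Step 2: worst case for a single result.** Drop k misclassified patients and no correctly classified ones. The count correct, x, stays the same and n falls to 57 − k.

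- No exclusions: 43/57 = 75.4%, P(X ≥ 43 | 57, 0.70) = 0.229, not significant.
- Four exclusions: 43/53 = 81.1%, P(X ≥ 43 | 53, 0.70) = 0.048, significant.

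**Step 3: worst case for the false-positive rate.** True accuracy is 0.70, there are 57 evaluable patients, and k misclassified patients are dropped before the same test.

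| k dropped | false-positive rate |
|---|---|
| 0 | 0.049 |
| 2 | 0.089 |
| 3 | 0.149 |
| 4 | 0.229 |
| 6 | 0.328 |

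**Step 4: dependence on selectivity.** If a fraction f of misclassified and g of correctly classified patients are dropped, true accuracy 0.70 appears as 0.70(1 − g) / [0.70(1 − g) + 0.30(1 − f)].

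- f = 0.1, g = 0: 72.2%
- f = 0.2, g = 0: 74.5%
- f = 0.3, g = 0: 76.9%
- f = 0.2, g = 0.1: 72.4%
- f = g = 0.2: 70.0%, no bias

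**Step 5: exclusions that depend on outcome but not on prediction.** Assume equal numbers of responders and non-responders, with 83% sensitivity and 90% specificity. Accuracy is 0.5 × 0.83 + 0.5 × 0.90 = 86.5%. Drop 30% of non-responders without regard to their prediction: (0.5 × 0.83 + 0.35 × 0.90) / 0.85 = 0.730 / 0.85 = 85.9%. Expected specificity stays at 90%, and accuracy moves slightly towards sensitivity, here downwards.

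**The case against.** Several stronger readings are tempting, and the documents do not support them.

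- **That the Year 1 and Year 2 clinical exclusions remove discordant patients.** A reader might infer this because the examples explain away poor outcomes. But the physician is not told the prediction, so a physician's exclusion can depend on the outcome and not on whether the prediction was right. Step 5 shows that losing non-responders in this way does not raise specificity and barely moves accuracy.
- **That the principal investigator sees both data sets.** This is pieced together from Study Setting, the follow-up text and Data Management; no sentence says it. The oversight section even states that no coordinating center will be established, which conflicts with the other sections.
- **That predictions are compared with outcomes at Year 1 while Year 2 is still open.** The text gives no timing for the comparison, no interim analysis is planned, and the endpoint is evaluated after 2 years.
- **That the blinding section shows the prediction is open to all.** That entry stands under assignment of interventions, beside other not-applicable entries, and most naturally refers to treatment. It is an ambiguity in wording, not evidence of bias.

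It can also be said that definitions of deviations and masked review usually belong in an analysis plan, which is not shown, and that some deviations, such as an invalid EEG montage, are visible at baseline. Both are fair. What remains is that the article itself declines to define a population and puts unmasked discretion in its place. Steps 2 and 3 are deliberately extreme: they subtract exclusions from the 57 meant for analysis and drop no correctly classified patient.

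**Conclusion.** The concern holds for the non-adherence rule. Undefined major deviations, judged case by case with no masking to the predicted class, leave the primary endpoint open to upward bias if the person deciding knows both prediction and outcome. The documents permit this; they do not show that it will happen. The direction is upward only if misclassified patients are dropped more often than correctly classified ones. On the worst-case assumption, four exclusions out of 57 are enough to turn p = 0.229 into p = 0.048, and the same number raises the false-positive rate from 0.049 to 0.229 at a true accuracy of 70%. The optional clinical exclusion at follow-up is a lesser problem: it makes the analysed set depend on outcome but, as far as the text shows, not on whether the prediction was correct. The sample size of 57 analysed and 114 enrolled is not in question.

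**What to change.** 1. In the non-adherence and missing-data section, define the primary set as all patients with a protocol-valid EEG prediction and a Year 2 outcome. Recordings that the EEG protocol does not allow stay out, and the pre-stated intolerance rule stays as written.
2. Move the discretionary exclusions (unexpected events at follow-up, and major deviations) to a sensitivity analysis.
3. List the major deviations in advance.
4. Have every exclusion decided and documented without knowledge of the predicted class, before predictions are linked to outcomes. Do that linkage after the Assessment 2 database lock.
5. In Who Will Be Blinded?, state that the entry refers to treatment, and that the predicted class is masked to patients and physicians (as the EEG section already says) and to whoever decides exclusions.

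The cost is wording and keeping the prediction file closed until lock. No extra staff or data are needed. Reported accuracy may come out somewhat lower than with discretionary exclusions.
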